### Sample size

The trial has been powered to detect an effect size of Cohen’s *d* = 0.50 for the comparison between iCT-PTSD and iStress-PTSD. This effect size was chosen as it corresponds to clinically meaningful differences on the primary outcome measure (PCL-5), and was used in the NICE [1] guidelines to define a clinically significant difference in placebo-controlled trials. For the comparison between psychological treatments and wait-lists an effect size of *d* = 0.80 is considered as clinically meaningful by NICE [1].

To detect a difference with an effect size of *d* = 0.50 with 80% power at *α* = .05, 63 participants per group are required. In addition, we have allowed for effects of clustering of observations within therapists, design factor = 1.18, assuming a conservative intra-class correlation of 0.01 (following Baldwin et al.’s recommendation [51]) and an average cluster size of 12 and a coefficient of variation of CV = .68, and conservatively allowed for 15% for drop-outs, yielding a sample size of 91 per group for this comparison [52]. Thus, as the initial allocation ratio is 3:3:1 (iCT-PTSD: iStress-PTSD: wait-list), 93 participants will be allocated to each of the treatment conditions, and 31 to the wait-list, and a total of 217 participants will be randomly allocated. The power to detect a difference between the treatments and wait-list conditions of *d* = 0.80 is greater than 98%.

### Allocation

After the eligibility assessment and giving informed consent for the trial, eligible participants will be randomised to one of the three trial conditions (iCT, iStress, wait-list) at a 3:3:1 ratio, stratified by location (Oxford, London, and Brighton and Hove), duration of PTSD (less than 18 months/18 months and above), and severity of PTSD symptoms on the PCL (high versus low), using an online random allocation programme developed by the Primary Care Clinical Trials Unit at the University of Oxford for this study. The programme uses a minimisation algorithm with a random component. The allocation sequence is not visible to the administrators who generate the treatment allocation with the programme.

For participants taking psychotropic medication, randomisation will take place after they have been on a stable dose for 1 month. For those currently receiving another psychological treatment, randomisation will take place after the end of this treatment. Participants originally allocated to the wait-list who have not recovered from PTSD at 13 weeks (end of wait) will be randomised to either iCT-PTSD or iStress at a 1:1 ratio.

### Blinding

Assessors of treatment outcome will be blinded. Therapists supporting the Internet-based treatments, trial administrators and participants will not be blind to treatment allocation due to the nature of the intervention.

### Recruitment

Recruitment will be mainly via referral from collaborating IAPT services (Buckinghamshire, Berkshire, Croydon, Lambeth, Lewisham, Oxfordshire, Southwark, Brighton and Hove, and East Sussex). Referrals from general practitioners (GPs) and other NHS services, such as Hospital Trauma Services or local therapists, are also accepted. Consent will be obtained for the GP or referring NHS service to be informed about the participants’ progress in therapy. Participants can also self-refer in response to information listed on the research team’s website (https://www.psy.ox.ac.uk/research/oxford-centre-for-anxiety-disorders-and-trauma/anxiety-disorders/post-traumatic-stress-disorder), trial registration websites (ISRCTN and UK Clinical Trials Gateway), or the University of Oxford’s trial website, email circulars at the collaborating site, and posters in GP practices, or media reports (such as local radio or newspapers) about the study.

### Data collection

Data will be collected from all participants, including those who discontinue treatment. Most of the outcome data will be collected via Qualtrics (anonymised by participant ID number), a widely used data collection software programme. If participants prefer, paper-and-pencil measures (anonymised by participant ID), these will be provided. Data for the process analyses will be captured online via the online therapy programmes (weekly measures). Access to the data will be restricted to named study personnel only and via a secure login (two-factor authentication).

The independent CAPS-5 assessors will receive comprehensive training in conducting and scoring the interview. Interrater reliability will be determined and discrepancies will be resolved by consensus.

In the event of source data being collected on paper, including the SCID-5 interview at the eligibility clinical assessment and the CAPS-5 interview at baseline (initial), 13, 26, 39 and 65 weeks, an exact copy of the anonymised data will be manually entered into the trial database by named study personnel, with the electronic data record being verified against the original paper record.

To aid retention, participants will be reimbursed £20 for completing each trial assessment at baseline, 6 weeks (including measures during treatment), 13 weeks, 26 weeks, 39 weeks and 65 weeks (see Fig. 2). They will not be paid for the clinical eligibility assessment and treatment.

Dropout, or premature termination from the study or treatment at any point after randomisation, will be recorded along with reason for discontinuation or termination. Participants can choose to withdraw from the trial intervention, withdraw from follow-up, withdraw from both aspects, or withdraw from both aspects and ask that previously collected data not be used. Their care in the NHS will not be affected at any time by declining to participate or withdrawing from the trial. A participant may be withdrawn from the intervention if they develop a condition which would exclude them from the study based on the eligibility criteria or a change in their clinical condition requiring urgent other treatment (e.g. the participant develops a psychotic disorder). Participants who withdraw/are withdrawn from the intervention part of the trial will continue in follow-up unless they withdraw their consent for this. Withdrawn participants will not be replaced.

Unless a participant has withdrawn consent to participation, repeated attempts using different approaches will be made to contact participants who cannot be easily contacted at assessment points. For any participant reluctant to complete the full outcome assessment at follow-up we will attempt to obtain the PCL-5, IES-R, PHQ-9, GAD-7, WSAS and ISI as a minimum dataset. As much information as possible will be collected from protocol non-adherers including reasons for non-adherence.

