The present study will compare a novel, trauma-focussed therapist-assisted online psychological therapy (internet-based cognitive therapy for PTSD, iCT-PTSD) and a comprehensive nontrauma-focussed therapist-assisted online psychological therapy (internet-based stress management therapy, iStress-PTSD). Both treatments will be compared with a wait-list to control for the natural recovery that is sometimes seen in PTSD samples.

Cognitive therapy for PTSD is a TF-CBT programme that has been shown to be highly effective and acceptable to patients [7, 17–20]. The treatment focusses on changing problematic appraisals that induce a sense of current threat, updating trauma memories and changing problematic behaviours that maintain the problem. A pilot study of an internet-delivered version of this treatment suggested that it may be as effective as face-to-face CT-PTSD [9].

Nontrauma-focussed CBT programmes for PTSD focus on teaching strategies that help patients cope better with PTSD symptoms, solve problems and reduce avoidance. The present study will use internet-based stress management therapy (iStress-PTSD), developed by Andersson and colleagues, a very comprehensive CBT stress-management programme that includes applied relaxation, mindfulness, thought challenging, and exposure to avoided situations. It has been shown to be effective in several randomised trials [8, 10]. The programme was translated into English and adapted for patients with PTSD.

The primary objective of the trial is to determine
Whether iCT-PTSD is superior to iStress-PTSD in reducing symptoms of PTSD

Other objectives are to determine
2.Whether iCT-PTSD and iStress-PTSD are efficacious, i.e. whether they lead to greater improvement in PTSD symptoms than a wait-list condition3.Whether iCT-PTSD leads to greater improvement in depression, anxiety, well-being, disability, quality of life and sleep problems than iStress-PTSD4.Whether iCT-PTSD and iStress-PTSD lead to greater improvement in depression, anxiety, well-being, disability, quality of life and sleep problems than a wait-list condition5.Whether iCT-PTSD is cost-effective compared with iStress-PTSD in terms of cost per participants with a clinical improvement in PTSD symptoms and costs per quality-adjusted life year (QALY) gained

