#### Measures for health economics analysis

The health economics analysis will use a measure of resource use, the Client Service Receipt Inventory (CSRI) [39]; the iMTA Productivity Cost Questionnaire (PCQ) [40]; two measures of quality of life, the EuroQol-5 Dimensions-5 Levels health survey (EuroQol EQ-5D-5 L) [41] (which is commonly used in health economic analyses but may be less sensitive to the effects of psychological interventions as most items refer to physical health) and the Endicott Quality of Life Scale (QoL) [37]; as well as employment status and state benefits. Treatment delivery costs will be calculated from therapist records of the number of minutes per week that the therapist spend messaging and talking with the participant.

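### The fallback minimum dataset gives the EQ-5D-5L no priority, although cost per QALY is a stated objective

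*Protocol article*

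**What the plan says.** Objective 5 (Background) asks whether iCT-PTSD is cost-effective against iStress-PTSD in terms of "cost per participants with a clinical improvement in PTSD symptoms and costs per quality-adjusted life year (QALY) gained". The Health economic evaluation section repeats both ratios as the form in which results will be reported, and leaves the details to a separate health economic analysis plan.

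Measures for health economics analysis names two quality-of-life instruments, "the EuroQol-5 Dimensions-5 Levels health survey" and the Endicott scale. It adds the CSRI for resource use, the PCQ for productivity, and employment status and state benefits. Treatment delivery costs come from therapist records.

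Data collection then sets a fallback. "For any participant reluctant to complete the full outcome assessment at follow-up", staff will try for six instruments: "we will attempt to obtain the PCL-5, IES-R, PHQ-9, GAD-7, WSAS and ISI as a minimum dataset". The next sentence adds: "As much information as possible will be collected from protocol non-adherers including reasons for non-adherence".

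**The concern.** A minimum dataset ranks what staff pursue when a participant will give only part of an assessment. This one covers the primary outcome, a second PTSD scale, depression, anxiety, functioning and sleep. It contains no input to the QALY. A QALY accumulates utility over time, so a visit without a utility leaves a gap that has to be imputed or interpolated, or the person is lost from that analysis.

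At stake is the information behind one numbered secondary objective. For people who stop at the minimum, the symptom comparisons keep their data at that visit and the cost-per-QALY comparison does not. The separate economic plan can say how missing utilities are handled, but it cannot recover values that were never requested. The order of collection is fixed in this document.

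**Working it through.** The plan states no figure on this point, so there is none to reproduce. The check has two parts.

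**1. Instruments needed for objective 5 against the fallback set**

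| Input to objective 5 | Source named in the protocol article | In the minimum dataset? |
|---|---|---|
| Utility for the QALY | EQ-5D-5L (implied by its listing; not stated in so many words) | No |
| Other quality-of-life measure | Endicott scale | No |
| Clinical improvement in PTSD symptoms | Criterion not defined in the article; PCL-5 or IES-R would serve, CAPS-5 would not | PCL-5 and IES-R yes, CAPS-5 no |
| Resource use | CSRI | No |
| Productivity | PCQ | No |
| Treatment delivery cost | Therapist records | Not needed; recorded separately |

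Both quality-of-life measures are absent, so the conclusion does not depend on which one is used for the QALY. For a participant who stops at the minimum:
- the cost-per-QALY ratio loses its effect input at that visit;
- the cost-per-improved-participant ratio keeps its effect input, provided improvement is defined on the PCL-5 or IES-R;
- both ratios lose survey-based costs and keep delivery costs.

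**2. Illustrative size at one visit**

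Inputs:
- Sample size section: 93 allocated to each active arm, so N = 93 + 93 = 186. Wait-list participants randomised to a treatment later are not counted.
- Sample size section: 15% allowance for drop-out.
- Assumption, not in the documents: a share r of participants gives only the minimum dataset at a given visit, with r from 5% to 15%.

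Number without a utility because of the fallback = N × r:
- r = 5%: 186 × 0.05 = 9.3, about 9
- r = 15%: 186 × 0.15 = 27.9, about 28

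If the planned drop-out is taken off first, 186 × 0.85 = 158.1 remain:
- r = 5%: 158.1 × 0.05 = 7.9, about 8 without a utility and 150 with one
- r = 15%: 158.1 × 0.15 = 23.7, about 24 without a utility and 134 with one

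**The case against.** The strongest reply is that the list is only a floor. Staff will attempt to obtain these six; nothing stops them from obtaining more. That stands. A reader might infer that the EQ-5D-5L will be missing by rule in everyone who falls back, and the text does not support this: the measure is given no priority, and it is lost only where a participant stops at the minimum. The request for as much information as possible helps less than it seems, because it concerns protocol non-adherers, who need not be the people reluctant to complete an assessment, and it ranks nothing.

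The list also has a visible rationale. The PCL-5 is primary, and the legend to Fig. 2 says that IAPT services require the IES-R, PHQ-9, GAD-7 and WSAS. The article itself warns that the EQ-5D-5L may be less sensitive to psychological treatment. These are good reasons to keep the listed scales and not to trade one away. They do not explain leaving out both quality-of-life measures. The ISI is not among the measures named as an IAPT requirement, and it is in the set.

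A reader might also infer that these utilities are especially unlikely to be missing at random, or that the losses differ by arm. The documents give no rate, mechanism or arm difference. Symptom, function and sleep scores from the same visit would be available as predictors, which makes missing at random easier to defend here than for people who give nothing.

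Finally, one might compound the loss over the follow-ups at 13, 26, 39 and 65 weeks: 1 − 0.95⁴ = 0.19 to 1 − 0.85⁴ = 0.48. That needs a different, independent set of people falling back each time, a complete-case analysis, and the EQ-5D-5L at all four visits. Reluctance probably persists within a person, which pulls the loss towards 5-15%. No section specifies complete cases, and the measure-by-visit schedule is in a figure that is not available here.

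**Conclusion.** The point holds as a modest, inexpensive improvement. The fallback set omits both quality-of-life measures although cost per QALY is a stated objective, so a participant who stops at the minimum gives no utility at that visit. This is a choice about collection, and the economic plan cannot undo it afterwards.

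The size is unknown. On the assumed 5-15%, about 9-28 of 186 would be affected at a visit. The benefit of a change is mainly better precision and less dependence on an imputation model. It would not remove a demonstrated bias, and the primary and clinical secondary comparisons are untouched.

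**What to change.** Add the EQ-5D-5L to the minimum dataset, directly after the PCL-5, and keep all six scales now listed. The cost is five items, about one extra minute (an estimate) for participants who are already reluctant, and a minor amendment to the follow-up procedure.

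This restores the utility input only. With the CSRI and PCQ still outside the set, survey-based costs for these participants would have to be imputed, or partly covered by a brief resource-use question if that is feasible. The economic plan should say which. If the sponsor prefers to leave the set as it is, a sentence giving the reason would be enough.

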### Data management

The trial staff will ensure that the participants’ anonymity is maintained. The trial will comply with the Data Protection Act, which requires data to be anonymised as soon as it is practical to do so. Participants will be identified by a participant ID number on outcome measures and any electronic trial database. Personal information will be kept separate from the trial data.

No interim analyses are planned. For statistical analysis, the anonymised data will be downloaded onto password-protected computers. Any changes made to the data will be stored in the audit log with a full history of changes being recorded. The final data file of the anonymised data will be accessible to the trial statisticians, health economist and principal investigators (PIs). It will be maintained by the trial statisticians and stored on a secure Oxford University server for 10 years post completion of the trial.

The internet programme supporting the online therapies was developed in collaboration with FRY-IT (https://www.fry-it.com). It has numerous security features representing current best practice. It will employ secure client-server communication, full encryption of the server database, enforcement of strong passwords, two-factor authentication (i.e. login requires both a password and a PIN sent to the participant’s mobile phone) and hosting on a tier-4 hosting server. External access to the database using SSH protocol is prohibited. The system has been subjected to industry-standard penetration testing.

### Statistical methods

#### Analysis of symptom and well-being measures

All analyses will be intent-to-treat from randomisation. The primary outcome measure will be the PCL-5 and the primary assessment point will be 13 weeks (end of weekly treatment calls/wait). Group comparisons on mean scores of primary and secondary symptom outcome measures will be performed with linear mixed-effect regression models. Both the main effects of repeated assessments and condition and their interactions are specified, and baseline scores are included as a covariate. Superior outcome will show in significant treatment condition or time x treatment condition interactions. All randomised cases will be included in the analyses, irrespective of missing data (mixed models and structural equation models account for data missing at random). Missing data mechanisms will be explored and reported.

The effect size for the primary research question will be categorised as statistically significant, trend for superiority (nonsignificant effect size of *d* = 0.25 and above), possible small superiority (nonsignificant effect size between *d* = 0.10 and *d* < 0.25), possible equivalence (nonsignificant effect size between *d* < 0.10 and *d* > − 0.10). Analyses will explore effects of location and therapist on outcome. A range of potential covariates will be considered, for example: duration of PTSD, age at trauma, trauma type, number of traumas, severity of physical consequences of the trauma, history of childhood trauma, comorbid major depression, comorbid anxiety disorder, substance use, SAPAS score, gender, education level, ethnicity. A complier-adjusted causal effect analysis (CACE) [53] will account for differences in participant adherence to the protocol. Details will be specified in a separate statistical analysis plan.

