## Methods/design

### Design

The design is a single-blind, randomised controlled trial comparing two therapist-assisted internet-based psychological treatments for PTSD and a wait-list condition (superiority trial), with an embedded process study. Assessors of treatment outcome will be blinded.

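### Non-significant primary results are labelled by point estimate alone: superiority-type wording exists in one direction only, and possible equivalence has no margin behind it

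*Protocol article*

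**What the plan says.** The rule is in the Protocol article under Statistical methods, Analysis of symptom and well-being measures. It begins "The effect size for the primary research question will be categorised as statistically significant, trend for superiority (nonsignificant effect size of" d = 0.25 and above). The next category is "possible small superiority (nonsignificant effect size between" d = 0.10 and below 0.25), and the last is "possible equivalence (nonsignificant effect size between" -0.10 and 0.10). There is no further category.

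The paragraph before it, in the same section, says that a superior outcome is shown by significant condition effects or significant time-by-condition interactions.

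The primary objective, in Background, is "Whether iCT-PTSD is superior to iStress-PTSD in reducing symptoms of PTSD". The Design section describes the trial as "comparing two therapist-assisted internet-based psychological treatments for PTSD and a wait-list condition (superiority trial"). The article gives no equivalence or non-inferiority margin.

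**The concern.** The rule has three weaknesses.

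- **Only the point estimate counts once the test has failed.** The labels do not depend on how precisely d is estimated, although the cut-offs of 0.10 and 0.25 are smaller than the trial's own margin of error.
- **The scale is signed but incomplete.** A lower bound of -0.10 is given, so negative values are contemplated. A non-significant d of +0.27 would be a *trend for superiority*, while -0.27 would have no description. The superiority-type labels therefore serve one arm only.
- **Possible equivalence rests on a small observed difference.** Equivalence needs an interval lying inside a margin. No margin is set and the trial was not sized for one.

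At stake is the wording of the primary comparison if it is not significant. That is a realistic outcome: 80% power at d = 0.50 leaves a 20% chance of it even if the target effect is true, and more if the effect is smaller.

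**Working it through.** **Inputs from the Sample size section.** Target d = 0.50 ("The trial has been powered to detect an effect size of Cohen’s" 0.50), alpha .05, power 80%; "63 participants per group are required"; "we have allowed for effects of clustering of observations within therapists, design factor = 1.18"; 15% drop-out; 93 allocated to each treatment arm.

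**The plan's own figure.** With a two-sided alpha, n = 2 × ((1.960 + 0.842)/0.50)² = 62.8, so 63 per group, as stated. A one-sided test would give 49.5, so about 50; two-sided alpha is therefore inferred. Inflation gives 63 × 1.18/0.85 = 87.5, or 64 × 1.18/0.85 = 88.8 starting from the exact t-test. The plan states 91. The gap is small and has no bearing here.

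**Analysed size.** Between 93 × 0.85 = 79 and 93 per arm.

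**Assumptions.** Positive d means iCT-PTSD better, inferred from the primary objective. The estimate of d is treated as normal with

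SE = √[(2/n) × D × (1 − ρ²)],

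where D is the design factor (1 or 1.18) and ρ the correlation of baseline with outcome. Baseline score is a planned covariate, but the article does not give ρ. I use ρ = 0 (unadjusted), 0.5 and 0.6. The result is non-significant when |d| < 1.96 × SE.

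**True d = 0, unadjusted (ρ = 0):**

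| n per arm | D | SE | 95% CI half-width | *Trend* | *Possible small superiority* | Both | *Possible equivalence* | No category |
|---|---|---|---|---|---|---|---|---|
| 93 | 1 | 0.147 | 0.287 | 1.9% | 20.4% | 22.3% | 50.5% | 22.3% |
| 93 | 1.18 | 0.159 | 0.312 | 3.3% | 20.7% | 24.0% | 47.0% | 24.0% |
| 79 | 1 | 0.159 | 0.312 | 3.3% | 20.7% | 24.0% | 47.0% | 24.0% |
| 79 | 1.18 | 0.173 | 0.339 | 4.9% | 20.7% | 25.6% | 43.7% | 25.6% |

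The remaining 5% are significant, 2.5% in each direction. They are ordinary type I error and are not counted against the labels.

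**True d = 0, with baseline adjustment.** The *Both* share is 19.1% to 22.7% at ρ = 0.5 and 17.2% to 21.0% at ρ = 0.6, over the same four rows. At ρ = 0.6, n = 79 and D = 1 the critical d is 0.249, so the *trend* category is empty.

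**What an observed value supports** (n = 93, D = 1, ρ = 0). An observed d of 0.25 has a 95% CI of -0.04 to 0.54; 0.10 has -0.19 to 0.39; 0 has -0.29 to 0.29. Even at an observed d of exactly 0 the interval reaches well beyond ±0.10. It still does with adjustment: at ρ = 0.6, SE = 0.117 and the half-width is 1.96 × 0.117 = 0.23.

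**Possible equivalence when a difference exists.** With true d = 0.25, the probability that the estimate falls between -0.10 and 0.10 is 14.5% (n = 93, D = 1) to 17.1% (n = 79, D = 1.18) unadjusted. At ρ = 0.6 and n = 93, D = 1 it is 9.9%. The overall range is about 10% to 17%.

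**The case against.** The strongest reply is that the labels are not claims of superiority. They say *trend* and *possible*, are each defined as non-significant, and the same section reserves a superior outcome for significant effects. That stands. A reader might infer that about a quarter of null trials would be declared superior, or that the labels set the trial's headline conclusion. The article says neither. What remains is that superiority wording is attached to results that fail the plan's own criterion.

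A second reply concerns size. The unadjusted figures ignore the planned baseline covariate, and adjustment brings the share to about a fifth. Most of it is the weakest label. Both points are right and are reflected in the range. It would also be wrong to say that the standard error exceeds every band: the equivalence band is 0.20 wide, against an unadjusted standard error of 0.15 to 0.17. The sounder comparison is of the CI half-width with the 0.10 limit.

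Third, the equivalence band is symmetric, so the one-sidedness belongs only to the two superiority-type labels and the missing negative category. No sign convention is stated. If it were reversed, the scheme would be equally one-sided towards iStress-PTSD. An incomplete list in a condensed article is no evidence of intent.

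Finally, details are deferred to a separate analysis plan. That covers what the article leaves open, such as whether confidence intervals will be reported, and their absence here is no finding. It does not cover cut-offs and labels that the article already fixes.

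**Conclusion.** The point holds as a defect in the interpretation rule. The labels depend on the point estimate alone among non-significant results, the superiority-type wording has no counterpart in the other direction, and *possible equivalence* has no inferential basis.

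Under no true difference, 22% to 26% of trials would receive a hedged superiority label without significance (17% to 23% with an assumed ρ of 0.5 to 0.6), and an equal share would go unlabelled. The figures rest on a normal approximation, 79 to 93 analysed per arm, a two-sided 5% test and the inferred sign of d. The absence of a negative category and of a margin is in the text and needs none of these assumptions.

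The primary test, its error rate and the sample size are sound on this point, so it is a should-fix matter.

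**What to change.** - Report the 13-week difference with its 95% CI and base the reading of a non-significant result on that interval, including whether it excludes the plan's own d = 0.50 in either direction.
- Drop *possible equivalence*, or state a symmetric margin with its justification and require the whole CI to lie inside it. A margin of 0.10 could not be met at this size under any of the assumptions above.
- If descriptive bands are kept, define them for both directions, state the sign of d, show them with the CI, and do not word them as superiority.

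This changes wording only, ideally before unblinded outcome data are seen; no data, design or sample-size change is needed. The cost is giving up favourable wording for a non-significant result.

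### Location and PTSD duration, on which allocation is minimised, are not committed terms of the stated outcome model but are left as exploratory or optional

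*Protocol article*

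**What the plan says.** **Allocation.** Under Allocation, participants are "stratified by location (Oxford, London, and Brighton and Hove), duration of PTSD" (cut at 18 months) and high versus low PCL severity, through a minimisation algorithm with a random component.

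**Analysis.** Under Analysis of symptom and well-being measures, the linear mixed model is given main effects of repeated assessments and of condition, their interactions, and the baseline score. The other design variables get a weaker status:
- location and therapist: "Analyses will explore effects of location and therapist on outcome";
- PTSD duration: "A range of potential covariates will be considered, for example: duration of PTSD", followed by 12 further candidates.

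The random effects are not stated. Details are left to a separate statistical analysis plan.

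**Sample size.** "we have allowed for effects of clustering of observations within therapists, design factor = 1.18". The Interventions section says that therapists are trained in both online treatments and have treated supervised cases in each.

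**The concern.** Minimisation makes the arms more alike on location and PTSD duration than simple randomisation would. If those factors predict the PCL-5 at 13 weeks, the treatment difference varies less from trial to trial. A model without them still counts their variance as residual noise, so its standard error is too large. The third factor, PCL severity, is largely covered for the primary outcome by the baseline PCL-5 score. The gap therefore concerns location and duration.

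Two things are at stake. One is a small amount of precision that the allocation scheme has already provided. The other is discretion: where the design factors have the same optional status as an open-ended covariate list, the primary estimate can depend on which adjustments are chosen once outcomes are known.

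**Working it through.** **Inputs from the article:** d = 0.50, power 80%, alpha 0.05 (sidedness not stated; two-sided reproduces the stated 63), design factor 1.18 (ICC 0.01, mean cluster size 12, CV 0.68), 15% drop-out, 93 per active arm.

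**Assumption:** the share R² of residual variance, after baseline score, that location and duration explain. The article gives no value; 2%, 5% and 10% are used.

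**1. The plan's own figure.** 2 × (1.96 + 0.8416)² / 0.50² = 62.8, so 63 per group, as stated. Then 63 × 1.18 / 0.85 = 87.5, so 88. Starting from the t-test size of 64 and rounding up at each step gives 90. The stated 91 is close to this, and nothing below depends on the difference.

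**2. Reference power.** Effective size per arm: 93 × 0.85 / 1.18 = 67.0. Noncentrality: 0.50 × √(67.0/2) = 2.894. Power: Φ(2.894 − 1.96) = 0.825, about 82%.

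**3. Actual size of the test when balanced factors are left out.** With perfect balance, the true standard error is √(1 − R²) times the one the model reports, so the actual alpha is 2 × [1 − Φ(1.96/√(1 − R²))].

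**4. Power with adjustment:** Φ(2.894/√(1 − R²) − 1.96).

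| Assumed R² | Actual alpha, factors omitted | Power, factors included |
|---|---|---|
| 2% | 0.048 | 0.832 |
| 5% | 0.044 | 0.844 |
| 10% | 0.039 | 0.862 |

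These are upper bounds on the effect for a given R², for two reasons:
- Minimisation with a random component does not balance perfectly.
- Under perfect balance the unadjusted test already gains a little power: Φ((2.894 − 1.96)/√(1 − R²)) = 0.831 at 5% and 0.838 at 10%. Against that reference, adjustment adds about 1.3 and 2.5 points, rather than the 2 and 4 points measured from 82%.

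**5. Therapist (secondary).** The usual formula gives a design factor of 1 + [(1 + 0.68²) × 12 − 1] × 0.01 = 1.165; the article states 1.18.
- If therapists were nested in arm and the model ignored them, alpha would be 2 × [1 − Φ(1.96/√1.165)] = 0.069, or 0.071 with 1.18. Simulation (15,000 runs, 79 analysed per arm, ICC 0.01) gives 0.069.
- If each therapist treats patients in both arms and differs only in overall level, simulation gives 0.047 at ICC 0.01 and 0.049 at ICC 0.05, so there is no inflation.

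**The case against.** **Deferral to the analysis plan.** The strongest defence is that the article leaves details to a plan that is not shown, and that covariates and random effects usually belong there. The model description names no random effect at all, not even participant, so it is not a complete specification. This stands to the extent that final omission is not established. It does not remove the point, because the article is not silent: it names location and duration and gives them exploratory or optional status. A plan that followed this wording would carry the mismatch forward.

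**Small and conservative.** Leaving out balanced factors makes the test slightly strict, so it cannot by itself produce a false claim of superiority. The power gain comes on top of power already above the 80% target, and the R² values are assumed. All of this stands and limits the weight of the point.

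**A stronger reading on therapist.** Because "we have allowed for effects of clustering of observations within therapists" while therapist is only explored in the analysis, a reader might infer that the primary standard error is too small and the 5% test really runs at about 7%. The article does not support this. That figure needs therapists nested in arm or treatment effects that vary by therapist. Training and supervised cases in both treatments point to therapists working across arms, although their allocation within the trial is not stated. The random effects are also unstated.

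**One combined fault.** A reader might also treat location, duration and therapist as a single defect in the standard errors. They are separate matters. Location and duration are minimised on but not sized for, while therapist is sized for but not minimised on. Any errors from leaving them out need not run in the same direction.

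**Conclusion.** The point holds for location and PTSD duration. Both shape the allocation, yet the article gives neither a firm place in the outcome model. If they predict outcome, the standard error of the primary contrast is somewhat too large: up to 1/√0.95 = 1.026 times the true value at R² = 5% and 1/√0.90 = 1.054 times at 10%. The sizes in the table rest on the assumed R² and on perfect balance. The concern about choosing adjustments after seeing the data does not depend on those assumptions.

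On therapist, only an inconsistency between the sample size section and the analysis section is established. No claim is made that the primary test is inflated. The point merits correction because the remedy is nearly free, not because the trial's conclusion is in danger.

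**What to change.** State in the analysis plan, and in the protocol at its next revision, that the primary model includes location (3 levels) and PTSD duration (under 18 months / 18 months and above) as prespecified fixed effects, alongside condition, time, their interaction and baseline PCL-5. Use the other listed covariates only in sensitivity analyses.

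For consistency with the sample size, name therapist as a random effect in the primary model.

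The cost is a wording change, 3 degrees of freedom (2 for location, 1 for duration) and one variance component. Both factors are needed at allocation, so nothing new has to be collected. No larger sample is needed: with the 1.18 allowance kept, power remains about 82% before any gain from adjustment.
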